**h) Planned Analysis:**

All ePAQ data are held on a secure password protected database. All data will be anonymised and transferred to SPSS for Windows (version 14.0), which will be used to carry out all statistical analyses. As the trial is a parallel group RCT, data will be reported and presented according to the revised CONSORT statement (Moher et al, 2001). The statistical analyses will be performed on an intention-to-treat (ITT) basis. All statistical exploratory tests will be two-tailed with P < 0.05. Baseline demographic data will be assessed for comparability between the treatment groups. Other secondary outcomes are to be assessed at baseline (randomisation) and at 6 months post randomisation. In the event of differences between the ePAQ and usual care groups with respect to baseline demographic, physical, and health-related quality of life measurements, multiple regression or analysis of covariance (ANCOVA) will be used to adjust the treatment effect for these variables. The ordinary least squares adjusted regression coefficient estimate for the treatment group parameter along with its 95% confidence interval (CI) will then be reported.

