**f) Randomisation**

Randomisation will occur on receipt of signed consent forms. Allocation will be through stratified block randomisation. SW will generate a randomisation schedule, for these strata, using the STATA software. This will be held remotely by GLJ (who will not be directly involved in recruiting patients to the study). By referring to the list, she will allocate patients to either the intervention group (ePAQ + telephone consultation) or the control group (usual care). The randomised allocation will then be passed on to the research nurse who will then send the relevant information packs to each participant, relating to the arm of the study to which they have been randomised.

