**1. Analysis of the PEQ**

The primary efficacy response variable is the outcome scale of the PEQ. The PEQ is to be posted to the subject immediately after the consultation with the clinician. A two independent samples t-test will be used to compare mean PEQ outcome scale scores between groups (ePAQ and usual care) in this parameter. A 95% confidence interval (CI) for the mean difference in this parameter between the ePAQ and usual care groups will also be calculated. Secondary efficacy outcomes are the other four scales of the PEQ: communication; emotion; barriers and auxiliary staff. These will be analysed in a similar way to the outcome scale.

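### The primary PEQ t-test omits the randomisation strata, and covariate adjustment depends on observed baseline differences, which costs some precision and leaves the rank of the adjusted estimate unclear

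*Protocol*

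**What the plan says.** Three parts of the protocol bear on this point.

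- **Section f) Randomisation:** "Allocation will be through stratified block randomisation". The section goes on to refer to the strata, but the text at hand does not name them.
- **Section h), 1. Analysis of the PEQ:** the primary comparison is unstratified. "A two independent samples t-test will be used to compare mean PEQ outcome scale scores between groups (ePAQ and usual care) in this parameter". The interval follows the same comparison: "A 95% confidence interval (CI) for the mean difference in this parameter between the ePAQ and usual care groups will also be calculated". No stratum term appears here or in any other analysis.
- **Section h) Planned Analysis, opening paragraph:** adjustment is conditional. "In the event of differences between the ePAQ and usual care groups with respect to baseline demographic, physical, and health-related quality of life measurements", then "multiple regression or analysis of covariance (ANCOVA) will be used to adjust the treatment effect for these variables". The result is to be shown as follows: "The ordinary least squares adjusted regression coefficient estimate for the treatment group parameter along with its 95% confidence interval (CI) will then be reported".

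The section on reducing bias also plans a comparison between the two consultants as a check for systematic differences. It does not put consultant into the model for the treatment effect.

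**The concern.** There are two linked weaknesses.

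1. **The strata are used in the design but not in the analysis.** Blocking within strata removes between-stratum variation from the difference in means. The t-test still counts that variation in its standard error. If the strata predict the PEQ score, the interval is wider than it need be and the test is conservative.
2. **Adjustment is driven by imbalance.** After proper randomisation, baseline differences arise by chance. Choosing covariates because they differ ignores whether they predict the outcome, which is what makes adjustment worthwhile. Whether an adjusted estimate exists, and for what it adjusts, is then known only after the data are seen. The protocol does not say which of the two results is primary if they disagree.

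At stake are precision on the primary outcome and a single, unambiguous primary estimate. The second matters more here because the trial cannot be blinded, and the protocol itself says that its clinicians are developing the service and regularly use ePAQ.

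**Working it through.** **Inputs from the protocol (section e and Table 1).** Difference 0.5, SD 1.0, two-sided 1% level, 90% power, 121 per group, 20% dropout, 304 randomised.

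**Reproducing the sample size.** By the normal approximation, n = 2(2.576 + 1.282)² × 1.0² / 0.5², about 119.0, so 120 per group. The noncentral t gives 121, as stated. For dropout, 121/0.8 = 151.25, rounded up to 152, and 2 × 152 = 304. The stated figure is right.

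**Effect of leaving out the strata.** Let R² be the share of PEQ variance that the strata explain. The protocol gives no value, so R² is assumed over a range.

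- Standard error used by the t-test: 1.0 × √(2/121) = 0.1286.
- True standard error under stratified allocation: 0.1286 × √(1 − R²).
- Ratio of the two: 1/√(1 − R²).
- True size: 2[1 − Φ(z/√(1 − R²))], with z = 1.960 at 5% and 2.576 at 1%.
- Power of the t-test at 1%: Φ[(0.5 − 2.576 × 0.1286)/(0.1286√(1 − R²))].
- Power of the stratum-adjusted analysis at 1%: Φ[0.5/(0.1286√(1 − R²)) − 2.576].

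Example at R² = 0.10: the true standard error is 0.1220. T-test power is Φ(1.384) = 0.917 and adjusted power is Φ(1.524) = 0.936.

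| R² (assumed) | SE ratio | True size, nominal 5% | True size, nominal 1% | Power at 1%, t-test | Power at 1%, adjusted |
|---|---|---|---|---|---|
| 0 | 1.000 | 5.0% | 1.00% | 0.905 | 0.905 |
| 0.05 | 1.026 | 4.4% | 0.82% | 0.911 | 0.921 |
| 0.10 | 1.054 | 3.9% | 0.66% | 0.917 | 0.936 |
| 0.20 | 1.118 | 2.8% | 0.40% | 0.929 | 0.962 |

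Both levels are shown because the sample size section uses 1% and the analysis section gives 5% for exploratory tests. Powers use the normal approximation.

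**How often the trigger would fire.** The protocol does not define a difference. If it meant p < 0.05 on k independent variables (both assumed), the chance of at least one is 1 − 0.95^k: 14% for k = 3, 23% for k = 5, 40% for k = 10.

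**Error rate of the conditional rule.** This was simulated with 242 patients, two strata, blocks of 4, five independent covariates and a p < 0.05 trigger. There were 20,000 runs per null scenario. Rejection rates are at nominal 5%; the pre-specified model contains the strata and all five covariates.

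| R² strata / covariates (assumed) | t-test | Conditional rule | Smaller of the two p-values | Pre-specified model |
|---|---|---|---|---|
| 0 / 0.2 | 4.9% | 4.4% | 5.3% | 4.9% |
| 0.1 / 0.2 | 3.9% | 3.5% | 4.3% | 4.9% |
| 0.1 / 0 | 4.1% | 4.2% | 4.3% | 5.2% |
| 0.2 / 0.3 | 2.9% | 2.2% | 3.1% | 5.0% |

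Power at 1% with R² of 0.1 and 0.2 (5,000 runs) was 0.91 for the t-test, 0.92 for the conditional rule, 0.93 with strata alone and 0.98 with the pre-specified model.

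**The case against.** **The direction is safe.** The t-test errs only towards caution, and not at all if the strata are unrelated to the PEQ score. Its power stays above the planned 90% in every row of the first table. This stands. A reader might infer from the mismatch between design and analysis that the primary p-value or interval is too optimistic. The documents do not support that: the interval can only be too wide.

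**The gain should not be overstated.** Setting 90% power against 92-94% compares an unadjusted test whose strata explain nothing with an adjusted test whose strata explain something. At the same R² the gain is 1 to 2 points. The larger gain, from 0.91 to 0.98, needs further covariates that explain 20% of the variance, which is also assumed.

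**The trigger frequency is not an error rate.** A reader might take 40% as a false-positive risk. It is the chance that adjustment is called for, under an assumed p < 0.05 rule and 10 variables; the protocol states neither. Even taking the better of the two p-values moved the error rate only from 4.9% to 5.3% where the strata explain nothing, and it stayed below 5% in the other scenarios.

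**The adjusted estimate may be only supplementary.** The PEQ subsection names one test, and the conditional sentence stands in general text that says only that the adjusted coefficient is reported. That is a fair reading, but the wording does not settle it. A covariate list could also be left to the SAP, and its absence is not the point. The point is that the protocol itself fixes a selection rule, which a SAP must follow or contradict.

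**Some wider remedies lack support.** Nothing in the protocol says that age predicts the PEQ. The planned consultant comparison is a legitimate check, and an arm-by-consultant interaction is a different question for which the trial was not sized.

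**Conclusion.** The point holds as a matter of efficiency and clarity. The protocol stratifies the allocation, analyses the primary outcome without the strata, and makes adjustment depend on chance imbalance without ranking the two estimates.

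If the strata explain 5% to 10% of PEQ variance, the standard error is 2.6% to 5.4% too large and about 1 to 2 points of power at the 1% level are lost. If they explain nothing, this part costs nothing. These figures rest on the assumed R² and on the planned 121 per group. Because the strata are not named in the text at hand, their true value cannot be fixed from the protocol.

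False positives are not materially inflated, and the trial's validity is not threatened. The change is worth making because it needs no patients, keeps the nominal error rate, and at worst gives up a trivial amount of precision.

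**What to change.** - In the PEQ subsection of section h), make the primary analysis a linear regression of the PEQ outcome scale on arm plus the stratification factors actually used in the randomisation schedule, and name those factors in section f). Add the consultant to whom the woman was referred, if that is not already a stratum; the recruitment section shows that it is known before randomisation. Report the arm coefficient with its interval.
- Fix any further baseline covariates before data are seen, because they are expected to predict the PEQ score, and use them whatever the baseline balance.
- Delete the baseline-difference trigger from the opening paragraph of section h).
- Keep the two-sample t-test as a supportive analysis and state that rank.
- Leave the between-consultant comparison in the section on reducing bias as it is. Label any arm-by-consultant interaction as exploratory.

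**Cost:** wording only. The sample size of 304 need not rise. The strata and the referred-to consultant are fixed by the time of randomisation, so they need no new data collection.

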**1. Analysis of the PEQ**

The primary efficacy response variable is the outcome scale of the PEQ. The PEQ is to be posted to the subject immediately after the consultation with the clinician. A two independent samples t-test will be used to compare mean PEQ outcome scale scores between groups (ePAQ and usual care) in this parameter. A 95% confidence interval (CI) for the mean difference in this parameter between the ePAQ and usual care groups will also be calculated. Secondary efficacy outcomes are the other four scales of the PEQ: communication; emotion; barriers and auxiliary staff. These will be analysed in a similar way to the outcome scale.

**2. Analysis of referral patterns**

At the 6 month follow-up we will measure (1) the number of referrals made for that patient and (2) the type of referral i.e. primary care (community nursing, community physiotherapy, GP, district nurse, practice nurse) and secondary care (gynaecology, urology, colorectal surgery, physiotherapy). The number of referrals over the 6-month follow-up will be described and tabulated. A two independent samples t-test will be used to compare mean number of referrals between the groups (ePAQ and usual care) in this parameter. A 95% confidence interval (CI) for the mean difference in this parameter between the ePAQ and usual care groups will also be calculated. The type of referral will be described and tabulated for each group. A chi-squared test will be used to compare referral patterns between the 2 groups (ePAQ and usual care).

**3. Analysis of the number of consultations**

The number and type of consultations over the 6-month follow-up period will be described and tabulated. An independent samples t-test will be used to compare mean number of consultations between the 2 groups (ePAQ in advance of clinic appointments vs usual care). A 95% confidence interval (CI) for the mean difference in this parameter will also be calculated.

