More recent development work has resulted in the creation of a website, where subjects can securely and anonymously access and use the ePAQ system via the Internet. This potentially allows subjects to use system in advance of clinic appointments (as opposed to the current practice of their completing it on arrival in clinic, immediately prior to their appointment). This study aims to evaluate the impact that using ePAQ in this way may have on the efficiency and quality of patient care. Initial survey data suggest that many women attending urogynaecology clinics do have access to the Internet and would be willing to use the system on-line & in advance of clinic appointments.4 The facility is also available in the Gynaecology Unit for women without Internet access to attend specifically for supervised use of the system. The in-depth assessment provided by the ePAQ may then be used to support an initial telephone consultation with a clinician, following which patients may be directed to the most appropriate clinic, as well as being provided with information and advice and have some forms of treatment initiated (such as behavioural therapy). The proposed randomised study aims to compare outcomes in women who use the ePAQ system in this way with women who undergo standard care in the Urogynaecology Unit.

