**iii) Cost & efficiency**

Outcome measures: Number & type of clinic attendances & consultations, Costs of prescriptions & investigations

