**Intervention Group: ePAQ clinic**

All women randomised to this arm of the study will be enetered onto the hospital PAS system under the ePAQ clinic. They will be invited by letter to complete epaq-online (and if necessary supervised ePAQ completion as a separate visit) and asked to contact Gynaecology Appointments in order to arrange their telephone consultation with AGF or SCR:

1. Letter inviting patients to complete epaq-online (including epaq-online information leaflet) & to telephone Gynaecology Appointments in order to book their telephone consultation.
2. Patient telephones Gynaecology Appointments when clerk will:
3. Ascertain whether patient has already succesfully completed epaq-online

If not: Agree & send a date, time & place to attend for supervised completion of ePAQ in hospital.

1. Agree & send (to all patients) a date, time & number for their telephone consultation
2. Scheduled telephone consultation with AGF or SCR

(supported by ePAQ report, referral letter and hospital casenotes)

1. Letter dictated to patient (including appropriate patient information leaflets & follow-up appointment)
2. Letter written to GP & referring clinician (including copy of above letter to patient)

The epaq-online information leaflet includes details of the web address for epaq-online (www.epaq-online.co.uk) with information explaining how to log-on and use the website. On completion of the questionnaire, the patient has the option of printing out a summary of her questionnaire data, which will include a summary of symptom scores in each area (urinary, bowel, vaginal and sexual). The patient is asked to forward her username and questionnaire ID to an STH email address ([contact]). Data are encrypted and anonymised (in line with good data protection practice) and can only be personalised to an individual patient by an approved clinician in receipt of the patient's username & questionnaire number, provided by the patient themselves. The clinician will use these results along with the patient's own casenotes and original referral letter to support the subsequent telephone consultation.

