**Non-intervention (control) group: Usual care**

All women randomised to this arm of the study will be given an appointment to attend the urogynaecology clinic. 'Usual care' currently includes the option of completing the ePAQ on arrival in clinic, immediately prior to the clinical consultation. As is currently standard practice, the results of the ePAQ will be used to inform & support clinical assessment, however, as the ePAQ is used *immediately* prior to the clinical consultation, patients cannot be triaged or receive any additional information on the basis of their questionnaire results.

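### The only test on consultations pools telephone and clinic contacts, so a fall in clinic visits of less than one per woman can be masked or can test as an increase

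*Protocol*

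**What the plan says.** Under section 3, aim iii, the protocol gives as an efficiency outcome "Number & type of clinic attendances & consultations". Type is therefore part of the declared outcome, and clinic attendances are named in their own right.

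The analysis section for this outcome (Planned Analysis, item 3) handles type descriptively: "The number and type of consultations over the 6-month follow-up period will be described and tabulated". Its one test is on an undivided count: "An independent samples t-test will be used to compare mean number of consultations between the 2 groups". The one confidence interval is for the same mean difference. The parallel items on referrals (item 2) and prescriptions (item 4) each add a chi-squared test on pattern. The item on consultations does not.

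The first contact differs between arms by design:
- **ePAQ arm** (Intervention Group: ePAQ clinic): the appointments clerk is to "Agree & send (to all patients) a date, time & number for their telephone consultation". The later steps include "Letter dictated to patient (including appropriate patient information leaflets & follow-up appointment". The Background describes the call as a step "following which patients may be directed to the most appropriate clinic".
- **Control arm** (Usual care): "All women randomised to this arm of the study will be given an appointment to attend the urogynaecology clinic".

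The protocol does not define a consultation for the purpose of the count. It calls the telephone contact a consultation throughout, and item 3 excludes no type.

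**The concern.** Aim iii asks whether questionnaire-supported telephone triage changes the use of clinic resource. The quantity tested adds the triage call to the clinic visits it may replace, one for one. Unless the call replaces at least one clinic visit per woman on average, the total will be higher in the ePAQ arm even when clinic visits have fallen. The trial could then report a significant p-value and an interval showing more consultations with ePAQ, with no pre-specified comparison of clinic attendances to set beside it.

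**Working it through.** **The plan's own figure.** The protocol gives no expected count or SD for consultations. Its sample size concerns the PEQ outcome scale: difference 0.5, SD 1.0, two-sided 1% level, 90% power. The normal approximation gives 120 per group and the noncentral t gives 121 (power 0.901; 120 gives 0.898). With 20% dropout, 121/0.8 = 151.25, rounded up to 152 per group and 304 in total. The stated 121 and 304 reproduce, and 152 per arm is used below.

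**Inputs from the protocol.** One scheduled telephone consultation per ePAQ-arm woman; a clinic appointment for each control woman; two-sided 5% for the exploratory tests; six months of follow-up.

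**Assumptions, not in the protocol.** The share p of ePAQ-arm women who still attend clinic; a common SD of 1.0, 1.5 or 2.0 for either count; all 152 women per arm analysed; every ePAQ-arm woman has exactly one call that is counted.

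**First step of the pathway, later care equal.**
- Total contacts: 1 + p (ePAQ) against 1 (control), a difference of +p.
- Face-to-face visits: p against 1, a difference of p − 1, which is a fall of 1 − p.

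**Over six months.** Let r be the mean fall in clinic visits per ePAQ-arm woman. The pooled difference is 1 − r. With equal later care, r = 1 − p.

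**Chance of a significant result.** SE = SD × √(2/152), which is 0.115, 0.172 and 0.229 for SD 1.0, 1.5 and 2.0. By normal approximation:
- P(significant rise in total) = Φ((1 − r)/SE − 1.96)
- P(significant fall in clinic visits) = Φ(r/SE − 1.96)

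Example, r = 0.5 and SD 1.5: 0.5/0.172 = 2.91; 2.91 − 1.96 = 0.95; Φ(0.95) = 0.83.

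Each cell gives the results for SD 1.0 / 1.5 / 2.0:

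| Fall in clinic visits, r | Pooled difference | P(significant rise in total) | P(significant fall, clinic visits alone) |
| --- | --- | --- | --- |
| 0.25 | +0.75 | 1.000 / 0.992 / 0.905 | 0.587 / 0.306 / 0.192 |
| 0.50 | +0.50 | 0.992 / 0.828 / 0.587 | 0.992 / 0.828 / 0.587 |
| 0.75 | +0.25 | 0.587 / 0.306 / 0.192 | 1.000 / 0.992 / 0.905 |
| 1.00 | 0 | 0.025 / 0.025 / 0.025 | 1.000 / 1.000 / 0.992 |
| 1.25 | −0.25 | 0.000 / 0.000 / 0.001 | 1.000 / 1.000 / 1.000 |

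The equal columns at r = 0.50 follow from symmetry (+0.5 and −0.5) and are not separate evidence. With 121 per arm, r = 0.50 gives 0.97 / 0.74 / 0.49 in both columns.

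**The case against.** **Stronger readings that do not hold.** A reader might infer that the ePAQ arm starts a whole consultation ahead by design. It does not: each arm begins with one first contact, by telephone or in clinic, and the excess is only the share p who also attend clinic. The follow-up appointment in the post-call letter makes some excess plausible, but the Background says only that women may be directed to a clinic, so substitution is open. A reader might also infer that the total moves against the saving. It does not: the pooled and face-to-face differences are p and p − 1, so they differ by a constant and fall together. The total is offset, not reversed.

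**Later care.** The count covers six months. Better direction to clinics, and advice or treatment begun at the call, could reduce later visits. The excess is then smaller, and it is zero or negative once r reaches 1. This stands, so the result is conditional.

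**Covered elsewhere.** Type is tabulated, and the economic analysis (Secondary Outcome Measures, item 5; Planned Analysis, item 5) costs ePAQ with telephone consultations against usual care. A fall in clinic visits would be visible in both. This stands too, but neither is a pre-specified between-group comparison of clinic attendances.

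**Definition of the count.** Equal weighting is inferred, because a consultation is undefined, and a statistical analysis plan that is not shown might define it. However, the protocol itself fixes the tested quantity as one undivided mean.

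**A face-to-face count alone is no better.** Its first-step difference, p − 1, cannot be positive, so it favours ePAQ by construction and leaves the consultants' telephone workload untested. This stands and shapes the fix.

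**Conclusion.** The point holds in a conditional form. The only test and interval for consultations are on a pooled mean that, on the natural reading, weights a telephone call and a clinic visit equally. Any fall in clinic visits averaging less than one per woman gives a higher pooled mean with ePAQ. For a fall of 0.5, the chance of a significant increase is 0.99 to 0.59 over an assumed SD of 1.0 to 2.0 with 152 per arm. Neither the SD nor the share still attending clinic is in the protocol, so these figures show scale and are not predictions. A higher total would be a true statement about total contacts; the error would lie in reading it as lower efficiency. This is a secondary, exploratory comparison, and the PEQ analysis and sample size are untouched.

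**What to change.** In Planned Analysis, item 3, say what counts as a consultation. State that the between-group difference and 95% CI will be given separately for face-to-face clinic consultations and for telephone consultations, alongside the total. Add that the total will not be read alone as the measure of efficiency. Keep the total in the analysis, because it is the one count that includes the telephone workload.

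The cost is a sentence or two and an additional secondary comparison. Type of consultation is already to be tabulated, so no new data are needed. The change brings the analysis into line with the outcome declared under aim iii.
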